## 7.5 REFERENCE SAFETY INFORMATION FOR PREDNISOLONE

### Undesirable effects:

The following safety information applies to prednisolone when used as an anti-inflammatory. As prednisolone will be used at low doses in this study as steroid replacement therapy, these undesirable effects are not expected.

The incidence of predictable undesirable effects, including hypothalamic-pituitary-adrenal suppression correlates with the relative potency of the drug, dosage, timing of administration and the duration of treatment (see “other special warnings and precautions”). Undesirable effects may be minimised by using the lowest effective dose for the minimum period, and by administering the daily requirement as a single morning dose or whenever possible as a single morning dose on alternative days. Frequent patient review is required to appropriately titrate the dose against disease activity. Anti-inflammatory/immunosuppressive: Increased susceptibility and severity of infections with suppression of clinical symptoms and signs, opportunistic infections, recurrence of dormant tuberculosis.

*Gastrointestinal:* Abdominal distension, acute pancreatitis, dyspepsia, nausea, increased appetite, oesophageal candidiasis, oesophageal ulceration, peptic ulceration with perforation and haemorrhage, perforation of the small bowel, particularly in patients with inflammatory bowel disease.

*Endocrine/metabolic:* Cushingoid facies, growth suppression in infancy, childhood and adolescence, hirsutism, impaired carbohydrate tolerance with increased requirement for antidiabetic therapy, menstrual irregularity and amenorrhoea, negative protein and calcium balance, suppression of the hypothalamo-pituitary adrenal axis, and weight gain. Although the frequency is not known, there is a risk for Cushing Syndrome.

*Fluid and electrolyte disturbance:* Hypertension, nocturia, hypokalaemic alkalosis, potassium loss, sodium and water retention, risk of congestive heart failure in susceptible patients.

*Musculoskeletal:* Avascular osteonecrosis, osteoporosis, proximal myopathy, tendon rupture, vertebral and long bone fractures, muscle weakness, wasting and loss of muscle mass.

*Dermatological:* Acne, bruising, impaired healing, skin atrophy, striae, telangiectasia.

*Neuropsychiatric:* A wide range of psychiatric reactions including affective disorders (such as irritable, euphoric, depressed and labile mood, and suicidal thoughts), psychotic reactions (including mania, delusions, hallucinations, and aggravation of schizophrenia), marked euphoria leading to dependence; aggravation of epilepsy, behavioural disturbances, irritability, nervousness, anxiety, sleep disturbances, and cognitive dysfunction including confusion and amnesia have been reported. Reactions are common and may occur in both adults and children. In adults, the frequency of severe reactions has been estimated to be 5-6%. Psychological effects have been reported on withdrawal of corticosteroids; the frequency is unknown. Intracranial pressure with papilloedema in children (pseudotumour cerebri) usually after treatment withdrawal, psychological dependence.

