## 7. PHARMACOVIGILANCE

### 7.1 DEFINITIONS

**Adverse Event (AE):** any untoward medical occurrence in a patient or clinical trial subject administered a medicinal product and which does not necessarily have a causal relationship with this treatment. An AE can therefore be any unfavourable and unintended sign (including an abnormal laboratory finding), symptom, or disease temporally associated with the use of an investigational medicinal product (IMP), whether or not considered related to the IMP.

**Adverse Reaction (AR):** all untoward and unintended responses to an IMP related to any dose administered. All AEs judged by either the reporting investigator or the sponsor as having reasonable causal relationship to a medicinal product qualify as adverse reactions. The expression reasonable causal relationship means to convey in general that there is evidence or argument to suggest a causal relationship.

**Unexpected Adverse Reaction:** an AR, the nature or severity of which is not consistent with the applicable product information (e.g. investigator's brochure for an unapproved investigational product or summary of product characteristics (SmPC) for an authorised product). When the outcome of the adverse reaction is not consistent with the applicable product information this adverse reaction should be considered as unexpected. Side effects documented in the SmPC which occur in a more severe form than anticipated are also considered to be unexpected.

**Serious Adverse Event (SAE) or Serious Adverse Reaction:** any untoward medical occurrence or effect that at any dose:

- **Results in death.**
- **Is life-threatening** – refers to an event in which the subject was at risk of death at the time of the event; it does not refer to an event which hypothetically might have caused death if it were more severe.

- **Requires hospitalisation, or prolongation of existing inpatients' hospitalisation.**
- **Results in persistent or significant disability or incapacity.**
- **Is a congenital anomaly or birth defect.**

Medical judgement should be exercised in deciding whether an AE/AR is serious in other situations. Important AE/ARs that are not immediately life-threatening or do not result in death or hospitalisation but may jeopardise the subject or may require intervention to prevent one of the other outcomes listed in the definition above, should also be considered serious.

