## 7.2 CAUSALITY

Most adverse events and adverse drug reactions that occur in this study, whether they are serious or not, will be expected treatment-related toxicities due to the drugs used in this study. The assignment of the causality should be made by the investigator responsible for the care of the participant using the definitions in the table below.

If any doubt about the causality exists, the local investigator should inform the study coordination centre who will notify the Chief Investigators. The pharmaceutical companies and/or other clinicians may be asked to advise in some cases.

In the case of discrepant views on causality between the investigator and others, all parties will discuss the case. In the event that no agreement is made, the MHRA will be informed of both points of view.

| Relationship          | Description                                                                                                                                                                                                                                                                                                         |
|-----------------------|---------------------------------------------------------------------------------------------------------------------------------------------------------------------------------------------------------------------------------------------------------------------------------------------------------------------|
| Unrelated      | There is no evidence of any causal relationship                                                                                                                                                                                                                                                                     |
| Unlikely       | There is little evidence to suggest there is a causal relationship (e.g. the event did not occur within a reasonable time after administration of the trial medication). There is another reasonable explanation for the event (e.g. the participant's clinical condition, other concomitant treatment).            |
| Possible       | There is some evidence to suggest a causal relationship (e.g. because the event occurs within a reasonable time after administration of the trial medication). However, the influence of other factors may have contributed to the event (e.g. the participant's clinical condition, other concomitant treatments). |

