## **7.4 REFERENCE SAFETY INFORMATION FOR HYDROCORTISONE**

### **Undesirable effects:**

*Blood and Lymphatic System Disorders:* Leucocytosis

*Immune System Disorders:* Hypersensitivity.

*Endocrine Disorders:* Increased or decreased motility and number of spermatozoa, menstrual irregularities, amenorrhoea, development of Cushingoid state, suppression of growth in children, secondary adrenocortical and pituitary unresponsiveness (particularly in times of stress, as in trauma, surgery, or illness), decreased carbohydrate tolerance, manifestations of latent diabetes mellitus, hyperglycaemia, increased requirements for insulin or oral hypoglycaemic agents in diabetes, hirsutism.

*Metabolism & Nutrition Disorders:* Sodium retention, fluid retention, potassium loss, hypokalaemic alkalosis, increased calcium excretion, negative nitrogen balance due to protein catabolism, weight gain, increased appetite.

*Psychiatric Disorders:* psychic disturbances, psychological dependence, insomnia. A wide range of psychiatric reactions including affective disorders (such as irritable, euphoric, depressed and labile mood, and suicidal thoughts), psychotic reactions (including mania, delusions, hallucinations and aggravation of schizophrenia), behavioural disturbances, irritability, anxiety, sleep disturbances, and cognitive dysfunction including confusion and amnesia have been reported. Reactions are common and may occur in both adults and children. In adults, the frequency of severe reactions has been estimated to be 5-6%. Psychological effects have been reported on withdrawal of corticosteroids; the frequency is unknown.

*Nervous System Disorders:* Convulsions, increased intracranial pressure with papilloedema (pseudotumour cerebri) usually after treatment, vertigo, headache, malaise.

*Eye disorders:* Posterior subcapsular cataracts, increased intra-ocular pressure, papilloedema, corneal or scleral thinning, exacerbation of ophthalmic viral disease, glaucoma, exophthalmos.

*Gastro-intestinal Disorders:* Peptic ulcer with possible perforation and haemorrhage, perforation of the small and large bowel particularly in patients with inflammatory bowel disease, pancreatitis, abdominal distension, ulcerative oesophagitis, dyspepsia, oesophageal candidiasis, nausea.

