### 8.3 SAFETY VARIABLES

The safety variables measured in this study are included as part of the secondary efficacy variable and are reproduced below:

- Safety
  - assessed by reporting of symptoms of steroid deficiency and myopathy and review of routine monitoring blood tests including full blood count (FBC), renal profile, liver function tests (LFTs), creatine kinase (CK), Adrenocorticotrophic hormone (ACTH) cortisol binding globulin (CBG) and bicarbonate.

In addition, the number of adverse events (AE), serious adverse events (SAE), and SUSARs (suspected unexpected serious adverse reactions) will be recorded for each Study Period.

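### The protocol's statements on expectedness conflict, so a related serious reaction listed for both drugs could be a SUSAR on prednisolone but not on hydrocortisone

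*Combined protocol and SAP*

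**What the plan says.** Four parts of protocol section 7 bear on expectedness.

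- **7.1 Definitions.** An unexpected adverse reaction is "an AR, the nature or severity of which is not consistent with the applicable product information". A documented effect that occurs in a more severe form than anticipated also counts as unexpected. A SUSAR must be a suspected reaction to the study drug, serious, and unexpected.
- **7.2 Causality.** The section opens with a forecast covering both drugs: "Most adverse events and adverse drug reactions that occur in this study, whether they are serious or not, will be expected treatment-related toxicities".
- **7.4 Reference safety information for hydrocortisone.** This is a plain list of effects, for example "Peptic ulcer with possible perforation and haemorrhage", with no restriction by dose or indication.
- **7.5 Reference safety information for prednisolone.** Before the list come two qualifying sentences. The first sets its scope: "The following safety information applies to prednisolone when used as an anti-inflammatory". The second reads: "As prednisolone will be used at low doses in this study as steroid replacement therapy, these undesirable effects are not expected".

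Under 7.3, the coordination centre notifies the MHRA, REC and sponsor of SUSARs within 7 days if fatal or life-threatening and within 15 days otherwise, and all investigators are told of every SUSAR. SAP 8.3 says that the number of "SUSARs (suspected unexpected serious adverse reactions) will be recorded for each Study Period".

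**The concern.** Expectedness is what separates a SUSAR from any other serious adverse reaction. A reference safety section exists to settle it, yet 7.5 supplies a list and in the same paragraph says that the effects on it are not expected. Hydrocortisone is also given here as replacement therapy, but its list carries no matching statement. Meanwhile 7.2 tells the investigator, before any event has occurred, that most reactions will be expected.

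At stake is whether the same serious reaction is handled alike on both drugs: whether it goes to the regulator and the ethics committee on the expedited timetable, and whether other investigators are told. Anyone who later split SUSARs by drug would also be comparing counts made under different rules.

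**Working it through.** No arithmetic applies. The check is to take a serious reaction that appears on both lists, assume it is judged related, and classify it under each reading of the text.

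**Reactions on both lists.** Perforated peptic ulcer, pancreatitis, vertebral fracture, tendon rupture, thromboembolism, congestive heart failure in susceptible patients and psychotic reactions appear in both 7.4 and 7.5. An effect on one list only is a different matter, because two products may legitimately have different lists.

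**Classification of a related perforated peptic ulcer.**

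| Reading | Hydrocortisone (7.4) | Prednisolone (7.5) |
|---|---|---|
| A. The 7.5 sentence is taken literally, as a statement of expectedness | Listed, so expected: not a SUSAR | Declared not expected: SUSAR |
| B. The 7.5 sentence is a clinical forecast, and 7.1 is applied to both lists | Listed, so expected: not a SUSAR | Listed, so expected: not a SUSAR |

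Under either reading, a form more severe than documented is unexpected on both drugs through the last sentence of that definition in 7.1. The readings differ only for prednisolone.

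**Which reading does the text favour?**

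1. For A: the sentence stands in a section headed as reference safety information, where expected is the operative regulatory term. The sentence before it limits the list to anti-inflammatory use, which suggests that the list is not the applicable information for replacement use.
2. For B: protocol 1.2 uses nearly the same phrase about bone and glycaemic effects of low-dose prednisolone, and there it plainly means not anticipated.
3. The first sentence of 7.2 leans towards treating reactions on both drugs as expected, so it sits badly with A. It also sits badly with 1.2, which calls the steroid risks minimal. It gives no test for classifying a single event.
4. 7.1 refers to the applicable product information but does not say whether the lists in 7.4 and 7.5 are that information at the doses used here.
5. The contents of the SAE form described in 7.3.2 include causality but not expectedness, so they do not settle the matter.

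No text available for this review says which statement governs. Two competent assessors could classify the same prednisolone event differently.

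**What depends on the classification.** The 7- and 15-day notifications, the circulation to investigators and the SUSAR numbers in SAP 8.3 depend on it. The 24-hour SAE report in 7.3 goes to the coordination centre and sponsor whether or not the event is expected, with exceptions unrelated to this point. SAP 9.7 tabulates AEs and SAEs by arm and period and lists every SAE, again without using expectedness. The efficacy analyses do not use it at all.

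**The case against.** The strongest reply is that there is only one rule. Section 7.1 defines expectedness, 7.2 is a forecast in a section about causality, and the 7.5 sentence is everyday language, as in 1.2. On that view, effects on both lists are treated alike and nothing is misclassified. Part of this stands: different handling is not forced, and 7.2 is not a classification rule. But the reply needs the reader to set aside the ordinary regulatory meaning of a word in the section written to fix that meaning, and to ignore the scope sentence before it. The ambiguity remains.

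Three stronger conclusions that a reader might draw are not supported.

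- *That the safety comparison is biased by construction.* The SAP plans no test of SUSARs between drugs. SAP 8.3 counts them by study period, and each period contains both drugs. SAP 9.7 is descriptive and does not use expectedness.
- *That about three participants per drug would be affected.* Both lists quote 5-6% of adults for severe psychiatric reactions, and with 55 participants 0.05 × 55 = 2.75 and 0.06 × 55 = 3.3. But severe is not the same as serious in the 7.1 sense, relatedness is also needed, no exposure time is given, and 7.5 itself says its list is for anti-inflammatory use. The rate cannot be carried over to four months of replacement treatment.
- *That the lists are defective because increased susceptibility to infection appears only under prednisolone.* Lists for two products may differ, and the trial's infection outcome comes from a questionnaire, not from SUSAR status.

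**Conclusion.** The concern holds as an unresolved contradiction in the protocol text. Read literally, a related serious reaction on both lists is a SUSAR on prednisolone and not on hydrocortisone; read as a forecast, it is a SUSAR on neither unless more severe than documented.

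The effect is confined to expedited reporting, notification of investigators and the comparability of SUSAR counts between drugs. The literal reading would produce more expedited reports on prednisolone, not fewer, and the six-monthly review by the data monitoring committee continues either way. No number of affected participants can be derived from the documents, and it may be very small. The point is still worth correcting before events have to be classified, because it governs a regulatory duty.

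This rests on one assumption: that the safety reporting flowchart and the pages not available for this review do not already state which rule governs.

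**What to change.** Reconcile protocol 7.1, 7.2, 7.4 and 7.5 with one explicit expectedness rule, applied in the same way to both drugs.

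1. In 7.5, replace the not-expected sentence with a statement of whether the 7.4 and 7.5 lists are the reference for expectedness under 7.1 at the doses used in this trial. If a restriction for replacement use is intended, put the same one on both lists. Which rule to adopt is for the sponsor to decide.
2. Delete the opening sentence of 7.2, so that causality and expectedness are judged event by event.
3. Optionally, add serious adverse reactions by drug to the tables in SAP 9.7. The SAP already lists the abbreviation SAR, and this count does not depend on expectedness.

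The cost is an amendment to the wording and, if the option is taken, one table row. Nothing changes for participants or procedures. The downside is a few more or fewer expedited reports, depending on the rule chosen.

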# Safety and Efficacy of Prednisolone in Adrenal Insufficiency Disease (PRED-AID Study) Protocol

**Ophthalmic:** Corneal or scleral thinning, scleral perforation, exacerbation of ophthalmic viral or fungal disease, glaucoma, increased intra-ocular pressure, papilloedema, posterior subcapsular cataracts, central serous chorioretinopathy (frequency not known).

**General:** Hypersensitivity including anaphylaxis, leucocytosis, malaise, thromboembolism.

**Withdrawal symptoms:** Too rapid a reduction of corticosteroid dosage following prolonged treatment can lead to acute adrenal insufficiency, hypotension and death. A “withdrawal syndrome” may also occur including arthralgia, conjunctivitis, fever, loss of weight, myalgia, painful itchy skin nodules and rhinitis.

## Safety Reporting Overview

[figure not shown]

## 8. ASSESSMENT AND FOLLOW-UP

**Length of study:** 9-month duration for each participant

### Study visits:

There will be 3 planned study visits, and 4 scheduled telephone consultations during each study period (total of 6 study visits and 8 telephone consults over both periods). The study visits will

be completed on Day 1 and Day 30 in the first month, and the final study visit of each treatment arm on Day 120. Telephone consultations will be on Days 8 and 15 in the first month, followed by further monthly consults on Day 60 and Day 90. Please refer to Appendix 2 for a schematic of the time and events on each study visit. The time window for completing each study visit is  $\pm 3$  days of the target date. Study visits which are completed outside of this window will require a protocol deviation form.

For each study visits, participants will be asked to attend the Clinical Research Facility at the Hammersmith Hospital at 0800h having fasted from 2200h the night before (permitting small sips of water only) and having taken their first steroid tablet of the day at least 2 hours prior. On arrival, observations including heart rate, blood pressure, weight and waist-hip circumferences will be recorded. Urine will be collected for measurement of additional bone markers. The urine will also be subjected to a pregnancy test in participants of child bearing potential. Routine safety blood tests, and immunological blood samples will be collected during each visit. Bone markers and glycaemic markers will also be measured. Participants will be asked to report any symptoms and to complete the SF-36, Addi-QoL and GNCQ questionnaires during each visit.

On the first day of each study period and during visit 1 (visit 4 in the second period), participants will take their usual baseline steroid replacement therapy. Participants will commence the blinded study medication from Day 2 until Day 120 (visit 3).

At the end of each study period, participants will be asked to return their remaining tablets, which will be used to gauge compliance.

## 8.1 LOSS TO FOLLOW-UP

In the instance that a participant is suspected to be lost to follow up, a member of the research team will initially attempt to make contact via telephone calls and email. After a reasonable attempt has been made to re-initiate contact, a letter will be sent to the participant by a study physician asking them to call, write or email the study team at their convenience within a week. If no response is received, a personalised letter will be sent to the participant's GP to inform them of the situation and in the interests of safety, to ask them to ensure that the patient has returned to their baseline steroid replacement therapy. In certain circumstances a phone call may be placed to the GP to advise them of the situation. The actions taken by the research team will be recorded in the participants NHS hospital notes.

The decision to withdraw a participant in these instances will be taken on a case-by-case basis by the Chief Investigator. If there are extenuating circumstances and the patient has continued their blinded medication, with the no compromise to the data collected and to the participant's safety, the participant may be permitted to continue on the study provided that they continue to consent. The Chief Investigator may opt to withdraw a patient if he feels that there is risk to the participant's safety or integrity of the data collected.

Data and samples collected on participants who are lost to follow up will be kept and used in the intention to treat analysis. The sample size calculation of 55 allows for a conservative 20% dropout rate. Participants lost to follow up will be replaced if required (where drop out exceeds 20%), to ensure the minimum power for analysis of this study is achieved.

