### Methods of data collection and analysis

Data will be collected and recorded throughout the study on both paper case record files and a validated database (Oracle InForm). Following last patient last visit and all data entry final data checks will be conducted. Post the resolution of any final data queries database lock will occur for analysis.

The analysis will follow the intention-to-treat principle and include all available data from participants within the treatment sequences to which they were randomised, regardless of treatment subsequently received.

As this is a two-period two-treatment crossover trial, the treatment effect will be estimated using a linear mixed effect model with participant as a random effect and fixed effects for treatment

and period, type of AI (primary vs secondary). Model assumptions, including the normality of residuals and random effects distributions will be assessed. If any assumptions are poorly met, then an appropriate transformation of the outcome (e.g. log transformation) will be considered.

Every effort will be made to obtain all follow up data for all participants, including those that have stopped treatment. The analysis method employs maximum likelihood estimation and is thus efficient for handling missing outcome data under a missing at random (MAR) assumption. Where appropriate sensitivity analyses will be conducted to check that the conclusions are robust for, example, to the missing data assumption. Although a washout period is incorporated into the design of the study to minimise carry-over effects, we will assess whether there is any evidence of a carry-over effect by fitting a separate linear mixed model which further includes the treatment by period interaction.

The continuous secondary outcomes will be analysed using the same modelling approach as specified above for the primary outcome. Where there are repeated measures of an endpoint within each period, we will display the effects over time and choose further appropriate statistical methods to assess any differences in the patterns over time. We will report compliance to study drug using data for pills missed doses over the study period. Adverse events will be tabulated by treatment group and period.

All treatment effect estimates will be reported with 95% confidence intervals and a two-sided 5% level of significance will be used. A detailed statistical analysis plan will be drawn up and agreed by the TSC prior to any unblinded data extraction.

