### **11.3 CONSENT**

Consent to enter the study must be sought from each participant only after a full explanation has been given, an information leaflet offered, and time allowed for consideration. Signed participant consent should be obtained. The right of the participant to refuse to participate without giving reasons must be respected. After the participant has entered the trial the clinician remains free to give alternative treatment to that specified in the protocol at any stage if he/she feels it is in the participant's best interest, but the reasons for doing so should be recorded. In these cases, the participants remain within the study for the purposes of follow-up and data analysis. All participants are free to withdraw at any time from the protocol treatment without giving reasons and without prejudicing further treatment, but will be encouraged to provide the reason, which will be recorded, if they are happy to do so. Participants who choose to withdraw will be encouraged to continue to provide outcome data for the remaining trial visits for the current treatment period, even though they may no longer be taking the blinded medication.

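### Protocol 8.1 ties staying in the study after lost contact to continued blinded drug, against the plan's own follow-up commitment, and its GP contact asks nothing about serious events

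*Combined protocol and SAP*

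**What the plan says.** Protocol 8.1 (Loss to follow-up) sets out the steps when a participant is thought lost: calls and email, a letter, then a letter to the GP. On who may stay, it says: "The decision to withdraw a participant in these instances will be taken on a case-by-case basis by the Chief Investigator". It describes one way to go on, which needs extenuating circumstances: "patient has continued their blinded medication, with the no compromise to the data collected and to the participant's safety, the participant may be permitted". Ongoing consent is also required. In the other direction, the person deciding "may opt to withdraw a patient if he feels that there is risk to the participant's safety or integrity of the data collected". Values already obtained from lost participants are kept for the intention-to-treat analysis, and participants are replaced if drop-out exceeds 20%.

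The letter informs the GP of the situation and makes one stated request: "in the interests of safety, to ask them to ensure that the patient has returned to their baseline steroid replacement therapy". A phone call to the GP is possible in some circumstances.

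Elsewhere the plan takes a broader line on follow-up. Protocol section 9 (Methods of data collection and analysis) says: "Every effort will be made to obtain all follow up data for all participants, including those that have stopped treatment". SAP 9.1 repeats this, and SAP 9.8 says much the same. Section 9, SAP 7.1 and SAP 9.1 analyse people as randomised, whatever treatment they received. Protocol 11.3 says that when a clinician gives alternative treatment, "the participants remain within the study for the purposes of follow-up and data analysis".

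**The concern.** Section 8.1 treats staying on study drug and staying under observation as one decision. For a re-contacted participant, adherence becomes part of the stated condition for further visits. That is a per-protocol criterion applied when data are collected, in a trial whose main analysis is meant to ignore adherence. People who stopped blinded drug and went silent may include some who did badly on one of the two drugs. If their Day 120 visits are not made, the missing-at-random assumption of the primary model is harder to defend for them.

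The safety side is separate. Protocol 1.1 and 1.2 name undertreatment and adrenal crisis as risks of replacement therapy and of switching, and a crisis could itself be why someone stops responding. SAE reporting under 7.3.2 starts when the site becomes aware of an event. For a participant who never replies, nothing in 8.1 creates that awareness. The DMC reviews safety data every six months, SAP 9.7 tabulates events by treatment and period, and the stopping rule in 8.2 turns on an event in more than three individuals. With counts that small, one or two unseen events could matter.

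**Working it through.** **Which provisions reach a re-contacted participant who stopped drug?**

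- *Protocol 8.1*: the only stated route to continue requires continued blinded drug. It does not say that data collection ends for others, but gives them no route.
- *Protocol 4.4*: encourages further data from someone who decides to withdraw, for the current treatment period only. It does not address withdrawal by the Chief Investigator under 8.1.
- *Protocol 11.3, alternative treatment*: keeps the person in follow-up, but covers a clinician's change of treatment, not stopping drug unprompted and then losing contact.
- *Protocol 11.3, withdrawal*: encourages outcome data even off blinded drug, but for those who choose to withdraw and only in the current period.
- *Protocol section 9, SAP 9.1 and 9.8*: cover everyone, including those who stopped, as a general intention. Section 8.1 is the specific procedure staff would follow.

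So the general commitment includes this group, and the specific procedure leaves it out.

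**What does the missing-data analysis cover?** SAP 9.8 adds a delta-adjusted multiple imputation for the primary outcome if more than 10% lack the Day 120 value. Counted over the 55 recruited, 0.10 × 55 = 5.5, so six or more. The planned drop-out, 0.20 × 55 = 11, would trigger it; five or fewer missing would not. Secondary outcomes are not covered. The text appears to apply the same δ in both arms. If so, the adjustment largely cancels from the treatment contrast when missingness is similar on the two drugs.

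**The plan's own figure.** Inputs from protocol section 9 and SAP 6.7: effect 1.5 µg/L, SD 3.0, correlation 0.5, 44 completers, two-sided 5%.

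- SD of the paired difference = 3.0 × √(2 × (1 − 0.5)) = 3.0
- Standard error = 3.0/√44 = 0.452
- Power = Φ(1.5/0.452 − 1.96) = 91.3%; with the noncentral t (43 df), 90.0%
- 44/(1 − 0.20) = 55

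The stated 90% power and the 55 both reproduce. The sample size is not in question.

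**Illustration 1: people back on usual treatment.** Assume 44 adherers with a mean paired difference of 1.5, and m re-contacted participants on their usual drug in both periods (difference 0). The intention-to-treat effect is 1.5 × 44/(44 + m). Leaving them out reports 1.50.

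| m | Effect with them (µg/L) | Shift if left out (µg/L) | Overstatement, m/44 |
|---|---|---|---|
| 2 | 1.435 | 0.065 | 4.5% |
| 4 | 1.375 | 0.125 | 9.1% |
| 6 | 1.320 | 0.180 | 13.6% |

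The shifts are 0.065/0.452 = 0.14 to 0.180/0.452 = 0.40 of a standard error.

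**Illustration 2: people who did differently on one drug.** If a share f of one treatment's Day 120 values is missing, and those values differ by g from the observed ones, the contrast from observed values alone shifts by f × g. Take g from 0.75 (half the design effect) to 2.4 µg/L (the largest short-term reduction the protocol cites from its pilot study).

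- f = 5%: 0.05 × 0.75 = 0.04 to 0.05 × 2.4 = 0.12 µg/L
- f = 10%: 0.10 × 0.75 = 0.08 to 0.10 × 2.4 = 0.24 µg/L

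The mixed model may recover part of this under missing at random. The values of m, f and g are assumptions; the documents give none of them.

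**The case against.** The strongest reply is that 8.1 is discretionary. It leaves withdrawal to individual judgement and describes one situation in which a person may continue; it never says that those who stopped drug must leave. It also keeps the data already collected, so Day 30 and completed-period values still enter a likelihood-based model. Other sections plainly intend follow-up off drug, SAP 9.8 offers a sensitivity analysis, and SAE reporting has no on-drug condition. The description of the GP letter does not limit what else it may ask.

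Much of this stands. A reader might infer that 8.1 bars non-adherers outright, that outcomes and serious events will go missing selectively, or that the intention-to-treat estimate becomes one for adherers only. The documents support none of these: the wording is permissive, retained data are analysed, and the general follow-up commitment remains in force. A reader might also want a numerical bound on missed serious events. An upper limit based on zero events describes people who were observed; it cannot measure what is lost in people who were not.

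What the reply does not remove is the inconsistency. Keeping earlier data does not supply a visit never made. Sections 4.4 and 11.3 do not clearly cover this group. Replacing drop-outs above 20% restores numbers but not the selected patients. The sensitivity analysis is limited to the primary outcome and to more than 10% missing. Awareness-based SAE reporting does not help where no step creates awareness.

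**Conclusion.** The point holds as an inconsistency to be reconciled and a risk to be closed. The stated route in 8.1 depends on continued blinded drug and allows withdrawal over data integrity, whereas section 9 and the SAP commit to following those who stop. Day 120 outcomes can be lost selectively as a result. Separately, no stated step brings serious events to light in a participant who never responds.

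The size is modest on the assumptions shown: about 0.07 to 0.18 µg/L against 1.5 µg/L for 2 to 6 people with zero paired difference in both periods. That case shows dilution, not bias from people who fared badly. Six would be more than half of the 11 expected drop-outs, each lost, found again and off drug, so it is a generous upper case. No figure can be put on the safety part from the documents.

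**What to change.** 1. **Separate the two decisions in 8.1.** Leave the decision on study drug with the Chief Investigator. Add a sentence such as: *A participant with whom contact is regained, and who consents, stays in scheduled data collection whether or not blinded medication was continued, at least for the current treatment period.* That minimum matches 4.4 and 11.3. Handle data-integrity concerns through deviation recording and the per-protocol set (SAP 7.2), not by ending follow-up.

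2. **Extend the existing GP letter or call, where consent allows.** Ask for vital status, hospital admissions and adrenal crises since last contact. Record answers with onset date, treatment and period. Protocol 7.3.2 exempts relapse and death due to adrenal insufficiency, and elective admissions for a pre-existing condition, from SAE reporting. So report as SAEs what that section requires and list exempt events separately. Report by treatment how many participants' status stays unknown.

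The cost is about two sentences in 8.1, a line in a letter already being sent, possibly a line in the consent form, and a few visits by people off study drug. Six such people attending both remaining visits of a period (Day 30 and Day 120) at £30 each would add at most 6 × 2 × £30 = £360 in participant expenses. No dose or clinical rule needs to change.
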